### Randomization and Masking

The decision to include patients in assignment groups will be made by the following randomization method: envelopes will be numbered on the outside with consecutive numbers, the assignment of the method in each envelope will be made randomly and consecutively using randomization software (http://www.randomizer.org/), and the envelope will be opened only in the operating room after verification of the fracture reducibility criterion. The randomization procedure will be delegated to a person who is not directly connected to the study.

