### Reducibility criteria

Fractures will be considered displaced if they show, before manipulation, loss of at least one of the criteria below. Fractures will be considered reducible if the radiographic parameters below [16,26] are achieved after manipulation under anesthesia (he contralateral side will be used as a reference):

– Radial length – accepted loss of up to 3 mm

– Radial inclination – accepted loss of up to 8°

– Volar tilt – accepted loss of up to 15°

– Ulnar variance – accepted difference of up to 2 mm

– Articular fragment with displacement – accepted up to 2 mm

Patients in the study will include those presenting a distal radius fracture of the 23A2, 23A3, 23C1, 23C2 or 23C3 types by the AO-ASIF classification and types II and III by the IDEAL classification that are displaced in the initial x-ray and can undergo closed reduction after manipulation under anesthesia.

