#### Method of surgical intervention

Surgery will be performed on an outpatient basis. Three surgeons will participate in the study who have been previously determined and confirmed to be familiar with the two surgical techniques used in the study. The surgical materials needed to perform the techniques will be available in the operating room for each surgery. After anesthesia, the patient will undergo manipulation and closed reduction of the fracture, and adequate reduction will be confirmed by the image provided by the image intensifier. Identification of the method to be used for each patient will be determined only after ascertaining that the fracture is reducible by the closed reduction technique, at which time the sealed envelope will be opened and the treatment technique that is to be employed will be revealed. Should the fracture not be reducible the patient will be excluded from the study.

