### Statistical methods

Epidemiological data will be collected (age, sex, type of fracture, time between fracture, and treatment). Standard deviations or confidence intervals, in the case of percentages, will be provided for each type of data. As a method for confirming randomization effectiveness, data will be compared when stratified by assignment group.

The assumption of normality will be verified by the Shapiro-Wilk test for the use of parametric tests. A Pearson’s chi-square test will be employed to analyze results from the two groups involving categorical variables. A Student’s (parametric) *t*-test will be used for comparing groups of numeric variables. Paired t-tests (parametric) and Wilcoxon tests (non-parametric) will be used to compare clinical progression at intervals of 2-, 8-, and 12-weeks PO and subsequently at 6- and 12-months PO. The significance level used in all statistical tests is to be 5% (alpha = 0.05), with tests having a P value less than 0.05 being statistically significant.

Should differences be found in primary outcomes, then statistical methods will be used to test whether there is robust correlation between epidemiological factors or fracture seriousness and the observed functional outcomes. In addition, we intend to employ Kaplan-Meier survival analysis to evaluate drop-outs should high rates of complications (greater than 20%) occur in either assignment group.

Patients who experience treatment failures and require additional surgery will be monitored and their results computed in the primary assignment group (intention-to-treat principle). Provisions are to be made for blinded statistical analysis of data by a statistician who is unfamiliar with the objectives and outcomes of interest.

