### Sample size calculation

The sample size was calculated based on a 10 point difference (10%) in the DASH between the two groups studied, assuming a 95% confidence interval, 80% statistical power and 20% sampling error, resulting in 36 patients in each group.

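### Fracture type (A versus C) is known before allocation, but the article neither balances it in the envelope series nor adjusts for it in the DASH comparison, so in 72 patients its mix is left to chance.

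*Protocol article*

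**What the plan says.** Under Randomization and Masking, the protocol article describes consecutively numbered envelopes and states that "the assignment of the method in each envelope will be made randomly and consecutively using randomization software". The envelope is opened in the operating room once reducibility has been verified. No stratum, block or minimization factor is named anywhere in the article.

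Under Reducibility criteria, eligible fractures are "23A2, 23A3, 23C1, 23C2 or 23C3 types by the AO-ASIF classification". Type is therefore an entry criterion. Under Initial treatment, the radiographic examination and the eligibility check come before the day of surgery.

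Under Statistical methods, type of fracture is among the baseline data to be collected, and the arms are to be compared on these data as a check on randomization. Groups are compared on numeric variables by Student's t-test with no covariate. Fracture seriousness is related to function only as a follow-up step, if a primary outcome has shown a difference.

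Under Sample size calculation, the target is a 10-point DASH difference, "resulting in 36 patients in each group".

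**The concern.** The article treats fracture type as worth knowing. It collects type, checks it for balance, and expects severity may relate to function. Yet the design does nothing in advance to balance type, and the main comparison takes no account of it. A check after randomization can reveal an imbalance but cannot correct one.

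The conditional step makes this worse in one direction. If a chance excess of the more severe fractures in one arm hid a real difference, the stated plan would not look at severity at all, because no difference would have been found.

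At stake are the precision of the DASH estimate and how convincing an unadjusted result would be if the arms turned out visibly different in fracture mix. The validity of the randomization is not at stake.

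**Working it through.** **Inputs from the article.** 36 per arm, 72 in total; target difference 10 DASH points; alpha 0.05; power 80%; 1:1 ratio (Abstract).

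**Assumptions, none in the article.** Two-sided test; type C share 50%, with 30% and 70% as a range; type C differs from type A by 5 or 10 DASH points within an arm.

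**1. The plan's own figure.** n per arm = 2 × SD² × (1.960 + 0.842)² / 10². The SD is not given, so 36 cannot be reproduced from the stated inputs alone. With SD 15: 2 × 225 × 7.849 / 100 = 35.3, rounded up to 36. Solving for SD at n = 36: 10 × √18 / 2.802 = 15.14, used below. The meaning of the 20% in "assuming a 95% confidence interval, 80% statistical power and 20% sampling error" is not explained. If it is an inflation for losses, the implied SD is about 13.5 to 13.8. Step 2 does not depend on the SD.

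**2. Chance of an uneven fracture mix.** Take 36 of 72 fractures as type C.

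- *Arm totals fixed at 36 and 36.* The number X of type C fractures in one arm is hypergeometric (72, 36, 36), and the gap in shares is |2X − 36| / 36. The variance of X is 36 × 0.5 × 0.5 × 36/71 = 4.56, so the gap has a standard deviation of 2 × 2.136 / 36 = 11.9 points. A gap of 15 points or more needs X ≤ 15 or X ≥ 21; a gap of 20 or more needs X ≤ 14 or X ≥ 22.
- *Simple randomization.* The type C and type A counts in one arm are independent Binomial(36, 0.5), and the gap is the difference between the two arms' type C shares.

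| Type C share | List | Gap ≥ 15 points | Gap ≥ 20 points |
|---|---|---|---|
| 50% | fixed 36/36 | 23.8% | 9.8% |
| 50% | simple | 19.6% | 8.4% |
| 30% or 70% | fixed 36/36 | 20.0% | 7.2% |
| 30% or 70% | simple | 16.2% | 7.1% |

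The result hardly depends on which kind of list was used.

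**3. What a gap would do to DASH.** Shift in the unadjusted difference = gap × effect of type. With a 20-point gap: 0.20 × 5 = 1 point, or 0.20 × 10 = 2 points. The standard error of the unadjusted difference is 15.14 × √(2/36) = 3.57, so a 2-point shift is about 0.56 of a standard error, or one fifth of the 10-point target.

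**4. What adjustment gains.** Share of variance explained by type = 0.25 × effect² / SD².

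- Effect 5: 0.25 × 25 / 229.3 = 0.027; power goes from 80.0% to 81.1%.
- Effect 10: 0.25 × 100 / 229.3 = 0.109; the standard error falls to 3.57 × √(1 − 0.109) = 3.37, and power rises to 84.3%.

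**The case against.** The best defence is that nothing here is an error. Unstratified randomization is valid and unbiased on average, and the t-test's error rate already allows for chance imbalance. The article gives no DASH values by fracture type, so a material effect of type is assumed. Type is at least compared between arms. All of that stands, and it confines the point to precision and chance imbalance.

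It can also be said that a journal article condenses a fuller protocol in which strata may be described. That stands too: the article shows one consecutive series and names no strata, but does not expressly rule them out. It does not rescue the analysis. If allocation were in fact stratified by type, the stratum would still belong in the comparison, and the stated t-test leaves it out.

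A reader might go further in two ways that the article does not support.

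- *Arm size left to chance.* The list type is not stated. A 1:1 ratio and 36 per group are stated, and a list with fixed totals fits the text as well as an unrestricted one. Even with an unrestricted list, power averaged over all splits would be 79.4% against 80.0% (SD 15.14), which is immaterial.
- *Surgeon imbalance.* The article says that "Three surgeons will participate in the study who have been previously determined", but not how a surgeon is matched to a patient or how many cases each would do. Any imbalance figure would rest on invented inputs. The absence of surgeon from a list of patient-level epidemiological data does not show that it goes unrecorded.

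**Conclusion.** The point holds as a modest design weakness. On the article's description, fracture type is known before allocation and is already collected, yet it is neither balanced nor adjusted for in the main DASH comparison. For type C shares of 30 to 70%, the chance of a between-arm gap of 15 points or more is roughly 16 to 24%, and of 20 points or more roughly 7 to 10%. The DASH consequence depends on an effect of type that the article does not give. At an assumed 10 points, a 20-point gap moves the estimate by 2 points, and adjustment would be worth about 4 points of power; at 5 points, both are small. The conclusion does not extend to bias, arm size or surgeon.

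**What to change.** In Statistical methods, replace the unadjusted t-test for the primary DASH comparison with a prespecified linear model containing treatment and fracture stratum (A versus C), fitted whether or not a difference is found. The stratum is already collected, so this needs no new data and uses one degree of freedom.

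If envelopes are not yet prepared, amend Randomization and Masking to use two series, one for type A and one for type C, each in permuted blocks of varying size that are concealed from the surgeons, and keep the stratum in the model. The cost is two stacks of envelopes instead of one, filled by the same outside person, and slight predictability at the end of a block. If envelopes already exist, the model alone is enough. A finer split over all five AO types is not advised: five strata would be thin in 72 patients.

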### Sample size calculation

The sample size was calculated based on a 10 point difference (10%) in the DASH between the two groups studied, assuming a 95% confidence interval, 80% statistical power and 20% sampling error, resulting in 36 patients in each group.

## Discussion

The results from this randomized clinical study are expected to be published in December of 2015. The objective of the study is to clarify the apparent lack of conclusive evidence regarding treatment of unstable fractures of the distal end of the radius.

## Abbreviations

AO: Arbeitsgemeinschaft für osteosynthesefragen foundation; ASIF: Association for the study of internal fixation; REC: Research ethics committee; DASH: Disabilities of arm, shoulder and hand; EPM: Paulista school of medicine; VAPS: Visual analog pain scale; E.F.: External fixator; L: Lateral; PA: Posteroanterior; PO: Postoperatively; VP: Volar plate; UNIFESP: Federal University of São Paulo.
